## Abstract

**Background:**

Ketogenic and low-glycemic-index diets are effective in treating drug-resistant seizures in children with Angelman syndrome. Cognition, mobility, sleep, and gastrointestinal health are intrinsically linked to seizure activity and overall quality of life. Ketogenic and low-glycemic diets restrict carbohydrate consumption and stabilize blood glucose levels. The ketogenic diet induces ketosis, a metabolic state where ketone bodies are preferentially used for fuel. The use of exogenous ketones in promoting ketosis in Angelman syndrome has not been previously studied. The study formulation evaluated herein contains the exogenous ketone beta-hydroxybutyrate to rapidly shift the body towards ketosis, resulting in enhanced metabolic efficiency.

**Methods/design:**

This is a 16-week, randomized, double-blind, placebo-controlled, crossover study to assess the safety and tolerability of a nutritional formula containing exogenous ketones. It also examines the potential for exogenous ketones to improve the patient’s nutritional status which can impact the physiologic, symptomatic, and health outcome liabilities of living with Angelman syndrome.

**Discussion:**

This manuscript outlines the rationale for a study designed to be the first to provide data on nutritional approaches for patients with Angelman syndrome using exogenous ketones.

**Trial registration:**

ClinicalTrials.gov, ID: NCT03644693. Registered on 23 August 2018. Last updated on 23 August 2018.

## Background

Angelman syndrome (AS) was first described in 1965 [1], and has a prevalence in the general population of 1:10,000–1:24,000 [2–4]. Loss or reduction of function of the maternal *UBE3A* gene (*ubiquitin protein ligase E3A)* was identified in the late 1990s as the causative mechanism in the majority of cases [5, 6]. Patients with AS universally have global developmental delays including speech impairment and movement disorders [7]. Individuals are typically described as having a happy disposition with frequent laughter. Eighty percent of patients also experience seizures, and all individuals with AS have a disordered electroencephalogram (EEG) [8, 9]. A large proportion of the population also has feeding problems (75%) and other gastrointestinal (GI) complaints [7, 10]. Unfortunately, AS has no cure. Typical treatment protocols include pharmacotherapy for seizures, physical and behavioral therapies, and educational interventions [11]. However, approximately 77% of the AS population experience treatment-resistant seizures [8].

Refractory epilepsy has been treated successfully with specialized dietary approaches, such as the ketogenic (KD), medium-chain-triglyceride (MCT)-based-, and low-glycemic-index diets (LGIT); these diets have also been successful in AS [12–15]. The KD allows the body to shift from carbohydrate-based metabolism to fat-based metabolism, thus stimulating hepatic ketogenesis. Nutritional ketosis is a state where the blood levels of ketone bodies are significantly above baseline, typically > 0.5 mmol/L. The ketone bodies (acetoacetate and beta-hydroxybutyrate (BHB)) are energy substrates used by mitochondria to produce adenosine triphosphate, and can be used as alternative fuels to glucose by the brain, heart, and skeletal muscles.

The high rate of refractory seizures, feeding and GI problems, and severe communication impairments in AS lead to a high unmet medical need. Overwhelming challenges exist to ensuring appropriate diets that serve the complex needs of individuals with AS. Nutritional approaches that promote the body’s use of ketones as an alternative fuel may improve overall nutritional status and allow for a liberalized dietary therapeutic strategy in individuals with AS and, therefore, improve quality of life.

Dietary supplementation with ketogenic ingredients is hypothesized to have an important impact on meeting the nutritional ketosis needs of patients with AS. Ketone supplements can aid in achieving and maintaining ketosis, improve the patient’s overall nutritional health in AS symptom management, and may improve quality of life for patients and their families. This study is designed as the first-ever to evaluate the safety and tolerability of the ketogenic ingredient beta-hydroxybutyrate in a patient population with a high rate of refractory epilepsy. This manuscript describes the rationale, methods, and potential importance of ketone-based nutritional interventions in children with AS.

### Objectives

The primary objective of the trial is to assess the tolerability of a nutritional formulation containing BHB in patients with AS aged 4–11 years on a variety of dietary backgrounds. The secondary objectives include assessment of ketosis when consuming the nutritional formulation and safety of the nutritional formulation in patients with AS. These outcome measures were chosen as this is a vulnerable, nonverbal population with limited ability to communicate difficulties with tolerability and safety concerns. Additionally, the degree of ketosis attained may inform future trials to assess the beneficial impact of patient nutritional status on health outcomes. All measures are assessed at baseline and the end of each 4-week intervention period (placebo versus test formulation).

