The study design for this nutritional intervention protocol is a randomized, double-blind, placebo-controlled, crossover study. There are two arms to the study, (1) an investigational formulation period followed by a placebo formulation period, or (2) a placebo formulation period followed by investigational formulation period. Each patient will receive both the investigational formulation and the placebo formulation, with a washout period between each arm. The randomization schedule was created by the Investigational Drug Service Pharmacy using randomization software in a 1:1 ratio with a block size of 4. Participants are enrolled in the next open slot of on the randomization table. The nutritional formulations are coded by the manufacturer lot number and, therefore, the clinical staff is blind to the actual contents of the container (active verses placebo).

Once randomized, subjects start Intervention Period 1, a 4-week period in which they receive nutritional formulation containing BHB or placebo while maintaining the diet noted at entrance into the study. Home monitoring occurs as indicated in Fig. 1. After 4 weeks of blinded intervention, subjects are evaluated in the clinic and then cease consumption of the ketone formulation or placebo for 4-week washout period. Following completion of the washout, subjects enter a second 4-week period in which they receive formulation versus placebo. They will continue the home monitoring throughout the duration of the study. Subsequently, at the completion of the second intervention, they undergo the final scheduled study visit and laboratory sampling. A washout period follows Intervention Period 2, and at approximately week 16 of the study, a follow-up call is made to the family to review symptoms and ensure the patient is not experiencing adverse events during this period. The trial schedule of enrollment, interventions, and assessments is outlined in Fig. 1 (FANS trial schedule of procedures).

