### Procedures and interventions

Background information regarding the subject’s natural history is collected using a REDCap© survey (Copyright 2006–2013 Vanderbilt University. All rights reserved) [16]. Body weight and height are measured at each study visit. Serum laboratory analysis is conducted to establish a metabolic baseline: comprehensive metabolic panel, complete blood count, ketones (beta-hydroxybutyrate and acetoacetate), and lipid panel. EEG, ERP and gait analysis using the ProtoKinetics Zeno™ Walkway are performed at each study visit (Fig. 1). The utility of ERP and gait analysis to predict changes in patient function in an Angelman population has not been clearly established, but their appropriateness in similar populations has been detailed elsewhere [17, 18]. Questionnaires completed during the study include the Vineland™-3, Developmental Behavioral Checklist (Pearson Education, Inc.), which has been used previously in studies of patients with AS [19], and the Callier-Azusa Scale to assess areas of motor development, perceptual abilities, daily livingskills, language development, and socialization. Dietary intake, seizure frequency, sleep, and GI health are evaluated throughout the protocol through at-home monitoring. Data collected during home monitoring is recorded on tablet devices provided to the parents/caregivers upon enrollment, preloaded with necessary tracking applications. Families are provided an EarlySense® monitor with a written guidance for home sleep monitoring. External sleep monitors are important in an AS population as wearable devices are typically removed by the patient. The monitors have not been studied with patients with AS; however, their validity has been demonstrated in the general population [20]. Urinary ketones are measured by the patient’s caregivers throughout the protocol, using Ketostix which are a validated measure of urine acetoacetate [21, 22].

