No studies testing ketone supplementation in patients with AS exist. Therefore, sample-size estimation is based on measures of ketosis. It is assumed from murine pre-clinical investigations, non-AS clinical studies using MCT and/or BHB, and low-carbohydrate dietary interventions, that the minimal change of the secondary outcome, degree of ketosis, from the baseline to the end of the fourth week of the investigational formulation intervention period will be 100% change from baseline (baseline for standard diet is typically < 0.5mmol/L of d-BHB in blood, or < 5 mg/dL acetoacetate in urine). The acetoacetate test used is Ketostix (Bayer Corp. Diagnostics Division, Tarrytown, NY, USA) which exhibits a sensitivity of 78% and a specificity of 96% when compared to a serum standard of 14.4 ml/dL. Considering a 25% drop-out rate, an estimate of 25 subjects need to be screened to achieve 15 completers.

Descriptive statistics, such as mean and standard deviation, are used to describe continuous variables, and frequency for the categorical variables. Means are compared using a paired two-sample *t* test. Statistical significance for all tests is *p* < 0.05. Multiple comparisons can be made including: (1) each subject to serve as their own control, comparing investigational formulation to placebo formulation, as well as to baseline, (2) each dietary background group considered in aggregate, comparing investigational formulation to placebo formulation, as well as to baseline, and (3) all subjects considered in aggregate, comparing investigational formulation to placebo formulation, as well as to baseline.

Any patient who receives the study formulation for any amount of time will be included in the intent-to-treat population for study analyses. Missing data points in this population will be addressed in discussion of any published results. Data from protocol-compliant participants is the defined population for efficacy subset analyses; any participant who received both protocol-required formulations and all required clinical assessments is considered protocol compliant. Such an efficacy subset analysis will be the primary approach for determining whether the trial endpoints are met. Those patients who complete the baseline visit, but do not start Intervention Period 1 and are withdrawn from the study, will be used for natural history reportable data only but will not be included in analyses for determining whether the outcome measures of the trial have been met.

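### Tests of the formulation against baseline are uncontrolled and would count time, growth and placebo response as a formulation effect; only formulation minus placebo should be tested

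*Protocol article*

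**What the plan says.** Objectives in the protocol article gives the assessment times: "All measures are assessed at baseline and the end of each 4-week intervention period".

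Study design gives the timeline:
- Period 1: "subjects start Intervention Period 1, a 4-week period in which they receive nutritional formulation containing BHB or placebo".
- Washout: after a clinic evaluation, children "cease consumption of the ketone formulation or placebo for 4-week washout period".
- Period 2: "subjects enter a second 4-week period in which they receive formulation versus placebo".
- End: a final visit closes Period 2, a further washout follows, and "at approximately week 16 of the study, a follow-up call is made to the family".

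The text describes no clinic assessment between the washout and Period 2, and defines no baseline specific to a period.

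Statistical considerations names a paired t test for means and sets p < 0.05 for every test. It then lists comparisons that may be made for the individual child, for each dietary group and for all subjects together, in each case "comparing investigational formulation to placebo formulation, as well as to baseline". The same section bases the sample size on the change in ketosis from baseline to the end of week 4 on the formulation. It also reads safety from changes in motor and cognitive function, height, weight and other measures.

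**The concern.** A test of the formulation against baseline has no concurrent control. Whatever else changes between the two measurements is counted as the effect. The children are 4 to 11 years old, so height, weight, and motor and developmental scores can move with time alone. Caregiver ratings can also move with expectation, and the article's own Discussion says that the placebo effect in Angelman syndrome is large.

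The crossover already contains a control for all of this, namely the placebo period. If the baseline contrast is tested beside the placebo contrast, at the same threshold and with no order between them, a significant change from baseline could be reported as a finding about the formulation when the placebo contrast shows nothing. The Discussion expects the results to guide further evaluations, so such a finding could carry forward.

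**Working it through.** **1. Timeline.** Period 1 (4) + washout (4) + Period 2 (4) + final washout (4) = 16 weeks. This reproduces the stated length, with the 2-week run-in outside the count.

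**2. Time from baseline to the end of the formulation period.**
- Formulation first: 4 weeks.
- Placebo first: 4 + 4 + 4 = 12 weeks.
- If the baseline visit is at the start of the run-in, which the text does not settle: 6 and 14 weeks.
- Mean for 15 completers split 8/7 (formulation first/placebo first): (8 × 4 + 7 × 12)/15 = 7.7 weeks.

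**3. Bias.** With drift of d per week and no treatment effect, the expected change from baseline is 7.7 × d. For d = 0.02, 0.05 and 0.08 SD of the change, that is about 0.15, 0.39 and 0.62 SD. These drift rates are assumptions; the article gives no drift rate and no SD.

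**4. How often the test is significant when there is no effect.** Simulation: 15 completers split 8/7, normal errors with unit SD, two-sided paired t test at 0.05. Repeat runs agree within about one percentage point.

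| Contrast | d = 0.02 | d = 0.05 | d = 0.08 |
|---|---|---|---|
| Formulation vs single baseline (4 or 12 weeks) | 9% | 28% | 57% |
| Same mean span for every child (7.7 weeks) | 9% | 29% | 61% |
| 4-week span for every child | 6% | 11% | 21% |
| Formulation minus placebo | 4.5% | 3.6% | 2.2% |

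The second row shows that unequal spans are not the cause: equal spans with the same mean reject as often or slightly more. The third row shows that shorter, equal spans reduce the error but do not remove it. In the fourth row the shared baseline cancels and drift nearly balances across the sequences. The rate falls below 5% because a plain paired t test leaves the period difference in its error term.

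**5. The same check in centimetres and kilograms (assumed growth rates).**
- Height, 4 to 8 cm a year: × 4/52 gives 0.31 to 0.62 cm; × 12/52 gives 0.92 to 1.85 cm.
- Weight, 1.5 to 3 kg a year: 0.12 to 0.23 kg over 4 weeks and 0.35 to 0.69 kg over 12.
- With an assumed SD of change in height of 0.5 to 1.5 cm, the single-baseline test is significant in 28% to 100% of trials with no effect. The lowest case agrees with step 4: 4/52/1.5 = 0.05 SD per week, 28%.
- At 6 cm a year and SD 1.0 cm, the single-baseline test gives 84%, a second baseline at week 8 gives 39%, and formulation minus placebo gives about 1%.

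**6. Residual drift in formulation minus placebo.** This is 8 × (difference in sequence sizes)/15: 0.53 week for 8/7, 1.6 weeks for 9/6 and 2.7 weeks for 10/5. It is small unless dropout is lopsided.

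**The case against.** Several points on the other side stand.

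- The list of comparisons is permissive: it says what may be compared, names the placebo contrast first each time, and belongs to a study described as exploratory. A reader might infer that the plan commits to testing against baseline at every level. It does not go that far. But any such test that is run falls under the 0.05 threshold, and nothing ranks it below the placebo contrast.
- A reader might blame the 4-week and 12-week spans, or the lack of a second baseline. The simulation does not support that: the cause is the uncontrolled before-after test.
- A reader might infer that the trial's main results are compromised. They are not. The primary outcome (formulation consumed against prescribed, early discontinuation, parent questionnaire) is not a change from baseline, and the placebo contrast does not depend on which baseline is used.
- A reader might extend the criticism to the sample size, because it rests on a change from baseline. That change is a 100% rise in ketosis, and the documents give no reason to expect ketones to drift much over these weeks.
- The drift rates are assumed. At 0.02 SD per week the excess is slight, and 0.08 means 12 × 0.08 = 0.96 SD by week 12.
- Fig. 1 is not shown and could list a contact at the end of the washout. Objectives and Study design describe no clinic measures then, and the third row of the table shows that an added baseline would leave the problem in place.

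**Conclusion.** The concern holds for the comparisons with baseline and no further. As allowed, they can present time, growth, learning and placebo response as an effect of the formulation. The error is material for secondary measures that drift: from near nominal (about 9%) to about 57% over the assumed range of drift, and 28% or more for height under the assumed growth rates and SDs. It is probably small for ketones, and it does not touch the primary outcome or formulation minus placebo. The sizes rest on assumed drift, growth and SD, 15 completers split 8/7, and a two-sided test; the article does not state sidedness. The direction does not depend on those values: any drift biases the baseline contrast. Severity is minor to moderate.

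**What to change.** In Statistical considerations, state that formulation minus placebo at the ends of the two intervention periods is the only tested contrast for conclusions about the formulation. Report changes from baseline descriptively, separately by sequence, without p-values, so that the 4-week and 12-week changes are not pooled as one quantity.

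A baseline taken from the end of the washout is not a substitute. Home data from that time should exist for some measures, since families are told "They will continue the home monitoring throughout the duration of the study" and urine ketones are measured by "caregivers throughout the protocol, using Ketostix". But a washout baseline still leaves 4 weeks of drift in the contrast. The visible text also does not establish a comparable home record before Period 1: it describes a 3-day recall at baseline, and urine ketones are not among the items listed for it.

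The cost is wording only. No visit, measurement or child is added, and the only loss is the p-values against baseline.

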Additional oversight and auditing of the trial is provided by [name], Chief Science Officer of Disruptive Nutrition, LLC with weekly conferences with members of the Vanderbilt research team. In-person meetings are planned quarterly, with data auditing semi-annually. A medical and research advisory committee has been established and consists of independent experts and key opinion leaders. The committee meets semi-annually. The Data Safety Monitoring Board is discussed in a separate section of this protocol under “Data Monitoring.”

Patients are recruited to the Nashville, Tennessee site at Vanderbilt University. Subjects with AS are recruited through the lead investigator’s practice, physician referrals, outreach through social media, and parent support groups such as the Foundation for Angelman Syndrome Therapeutics and the Angelman Syndrome Foundation. Subjects are enrolled with the following inclusion criteria: genetically confirmed diagnosis of Angelman syndrome; age 4–11 years; currently on a LGIT, KD (conventional 4:1 or 3:1, MCT, modified Atkins), or standard diet (regular diet) consistently for at least 3 months; willingness to consume the investigational formulation; and willingness to undergo protocol examinations at home and clinic visits. Subjects are excluded if they: require parenteral nutrition; have major hepatic or renal dysfunction; have a history of diabetes or have diabetes; are significantly underweight with a body mass index < 18.5; participate in other clinical intervention studies within 1 month prior to entry to the study; are unwilling to comply with the protocol requirements; or have contraindications for the use of ketogenic or low-carbohydrate diets which, in the opinion of the investigator, may influence a patient’s ability to participate in the study. Subjects are permitted to continue using all previously prescribed medications, provided the prescriptions have not changed in the 1 month prior to randomization. Parents/guardians of all eligible subjects must sign informed consent prior to study enrollment, following adequate explanation of the aims, methods, objectives, and potential hazards of the trial by the responsible investigator (see Additional file 3).

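### The underweight exclusion applies one fixed body mass index cut-off of 18.5 to children aged 4–11, which as written would remove most normal-weight children

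*Protocol article*

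**What the plan says.** The eligibility paragraph of the Methods, just before the Study design section, lists among the inclusion criteria "genetically confirmed diagnosis of Angelman syndrome; age 4–11 years". The Objectives section repeats the age range, describing the target as "patients with AS aged 4–11 years on a variety of dietary backgrounds". The same eligibility paragraph then excludes subjects who "are significantly underweight with a body mass index" below 18.5. That number is the only definition of underweight in the article. It carries no adjustment for age or sex and no centile or z-score.

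The Statistical considerations section sets the recruitment plan: "Considering a 25% drop-out rate, an estimate of 25 subjects need to be screened to achieve 15 completers".

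**The concern.** A single absolute BMI cannot mean significant underweight at both age 4 and age 11, because the BMI distribution shifts across those years and differs by sex. If typical values at these ages lie below 18.5, as the assumed references in the working have it, the criterion does not pick out thin children. It removes ordinary ones and keeps the heavier tail.

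Two things are at stake. The first is feasibility: 15 completers cannot come from 25 screened if one criterion removes most candidates. The second is who the result describes. The primary objective is tolerability, compliance is measured as the amount consumed against the amount prescribed, and serving size follows body weight. The Background reports feeding problems in 75% of the Angelman population. A sample restricted to heavier children would say little about that population. If staff instead disregard the number, the trial enrols children who meet a written exclusion criterion.

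**Working it through.** **Inputs from the protocol article.** Threshold: BMI below 18.5 (unit taken as kg/m²). Age: 4–11 years. Recruitment plan: 25 screened, 25% drop-out, 15 completers. The threshold is stated without derivation, so there is no plan figure to reproduce.

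**Step 1. What the rule demands (no outside data).** Minimum eligible weight = 18.5 × height².

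- 1.00 m: 18.5 × 1.00 = 18.5 kg
- 1.10 m: 18.5 × 1.21 = 22.4 kg
- 1.20 m: 18.5 × 1.44 = 26.6 kg
- 1.30 m: 18.5 × 1.69 = 31.3 kg
- 1.40 m: 18.5 × 1.96 = 36.3 kg

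**Step 2. Share excluded, normal approximation.** The article gives no BMI distribution. Assumed: median 15.5–17.5 and SD 1.5–3 over ages 4–11. Share below 18.5 = Φ((18.5 − median)/SD).

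- Median 15.5, SD 1.5: Φ(2.00) = 97.7%
- Median 16.5, SD 2: Φ(1.00) = 84.1%
- Median 17.5, SD 3: Φ(0.33) = 63.1%

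**Step 3. Share excluded, by age.** A second assumed reference, also not in the article, uses 5th, 50th, 85th and 95th centiles for each year of age. Its medians are about 15.4–15.6 at ages 4–7, rising to 17.2 at age 11. Its 85th centiles are about 16.8–17.4 at ages 4–7, rising to 20.2 at age 11. Interpolating on log BMI and weighting ages equally, the share still eligible is about 2% at age 4, 5% at 6, 11% at 8, 24% at 10 and 32% at 11. The mean is 12.4%, so about 88% are excluded.

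As a sensitivity check the whole BMI distribution was shifted. Normal weight means between the unshifted 5th and 85th centiles; overweight means at or above the unshifted 85th. Completers = eligible × 0.75.

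| Shift (kg/m²) | Eligible | Normal-weight excluded | Overweight among eligible | Eligible of 25 | Completers |
|---|---|---|---|---|---|
| −0.5 | 9.5% | 96.8% | 74% | 2.4 | 1.8 |
| 0 | 12.4% | 95.9% | 73% | 3.1 | 2.3 |
| +1 | 21.2% | 93.7% | 80% | 5.3 | 4.0 |
| +2 | 36.8% | 87.5% | 84% | 9.2 | 6.9 |
| +3 | 60.9% | 68.8% | 88% | 15.2 | 11.4 |

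At zero shift, the overweight share of eligible children is 100% at ages 4–8, 94% at 9, 64% at 10 and 47% at 11.

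**Step 4. Against the recruitment plan.** Fifteen completers at 25% drop-out need 15/0.75 = 20 enrolled. All eligibility criteria together may therefore remove at most 5 of 25, or 20%. For this criterion alone to remove no more than 20%, the median BMI would have to be at least 18.5 + 0.842 × SD: 19.8 at SD 1.5, 20.2 at SD 2 and 21.0 at SD 3. All lie well above the assumed medians.

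Under step 2, 25 screened gives:

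- 25 × 0.023 = 0.6 eligible at the severe end
- 25 × 0.159 = 4.0 in the mid-case (about 3 completers)
- 25 × 0.369 = 9.2 at the favourable end (about 7 completers)

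**The case against.** The strongest point is that no figure in the article supports the size of the effect. The BMI distributions are assumed and describe children in general, and the article gives no BMI data for Angelman syndrome. That stands, and it is why the result is a range. The direction did not change at any value tried, including a shift of +3 kg/m².

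The criterion could also be read as two conditions, so that a child must be judged significantly underweight and also fall below 18.5. On that reading a normal-weight child is not excluded. But the number is the only definition given, and if unstated judgement decides, the criterion can be neither reproduced nor audited. Either way the wording needs repair.

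The article condenses a fuller protocol, and an age-specific qualifier may have been lost. That may explain the text, but it does not excuse a specific threshold that is printed and does not fit the age range beside it.

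Some limits on the consequences are fair. Each child receives both products, so a heavier sample would not by itself bias the formula-versus-placebo contrast; the damage is to feasibility and generalisability. The 25 to be screened is an estimate rather than a cap, and families consented remotely before the baseline visit may not be an unselected sample. Those left are mainly overweight overall and at ages 4–10, but only about half are at age 11.

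**Conclusion.** The criterion is wrong as written and must be corrected. The mismatch between a single BMI cut-off and an age range of 4–11 years is plain from the article, and the minimum weights follow by arithmetic. How many children are lost depends on assumed BMI distributions: 63% to 98% of unselected children on the normal approximation, and about 88% on the age-specific centiles. On those centiles about 96% of normal-weight children are excluded, and 69% still are if every BMI is raised by 3 kg/m². At 63% exclusion, 25 screened gives about 9 eligible children, short of 15 even before drop-out. Only the extreme +3 shift reaches about 15 eligible, still below the 20 that the plan's own drop-out rate requires.

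**What to change.** Replace the fixed cut-off with an age- and sex-specific definition that matches the stated intent of excluding significantly underweight children: BMI-for-age below a low centile or z-score on a named growth reference. The investigators should choose the reference and the limit. State whether clinical judgement may add to or override the number. If any children have been enrolled with a BMI below 18.5, say how they were handled under the existing text.

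The cost is a one-line eligibility amendment and its submission to the IRB. Height and weight are already measured at each study visit, so no new data are needed, and recruitment becomes easier.
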